### Data management

LH will be responsible for data collection under supervision of the corresponding author VP, who is the principal investigator and responsible for the project management in general. All data on paper will be stored in a locked, secure area at Tilburg University. Digital data will be stored in a project data package, according to the data management guidelines of Tilburg University. Patient identifiable data (e.g., contact information and informed consent forms) will be stored separately from anonymized data. Patient confidentiality will be protected in line with the ethics guidelines of Tilburg University and the University of Amsterdam.

Data will be analyzed by LH after trial completion and no interim analyses will be done. Data will not be released before completion of the trial. Data (anonymized) will be shared directly after publication with restricted access, which means that data may be made available on reasonable request from the corresponding author VP.

### Trial status

As of 20 February 2020, the study is recruiting participants, with 28 enrolled so far.

## Discussion

Current study’s objective is to test the effectiveness of an online MBI in pregnant women with pregnancy distress. For this purpose, we will compare an intervention group with a control group who receives care as usual. The primary outcome is a decrease of pregnancy distress, i.e. symptoms of depression and anxiety. Secondary outcomes are potential working mechanisms, such as mindfulness skills, rumination and self-compassion. Tertiary outcomes are obstetric data like gestational age at birth, use of anesthesia, mode of delivery and birth weight in relation to changes of distress symptoms.

The current study has both strengths and limitations. Strengths of the study include the randomized controlled design and the expected sample size of 119 women in the intervention group. The current study is part of the Brabant Study, a large longitudinal birth cohort study among 4000 pregnant women, which makes inclusion of eligible women easily feasible. A limitation of the study is that the secondary outcome variables, the potential working mechanisms, can only be explored in the intervention group. The control group will fill out the questionnaires of the Brabant Study only, in which mindfulness skills, rumination and self-compassion are not measured.

Because there is a need for randomized controlled trials with sufficient power evaluating the effect of MBIs during pregnancy on maternal mental health [30–33], the current study is clearly of added value, and is expected to increase knowledge about the effectiveness of online MBIs during pregnancy in women with pregnancy distress. Furthermore, the current study will contribute to the knowledge of potential working mechanisms in MBIs, since reviews suggest changes in mindfulness skills, rumination and self-compassion to be associated with or to mediate the effect of MBIs on stress, anxiety and depression [23–25], but no definite conclusions can be drawn yet [23].

An essential part of the study is that the outcome of the current study (e.g., an online MBI with proven effectiveness to reduce distress in pregnant women) should be disseminated over the whole country. As a consequence, we will focus on the distribution of study results and derived knowledge through the following five different approaches. First, all steps that are necessary to implement this program within perinatal care will be carefully registered during the study, taking into account problems encountered during the set-up of the program. This will result in a general guidelines book at the end of the study. Special attention will be given to obstacles in the procedure and obstructive and promoting factors. Second, in the local area, the consortium structure and its collaborators (including midwifes, obstetricians and maternity care-workers) will be used to inform all healthcare workers about the online MBI course. For this purpose, we have a budget to further reinforce the set-up of a center of knowledge and excellence within the local consortium. This will contribute to setting up an infrastructure that will persist in the future to improve perinatal care. The members of the local consortium will be visited and instructed how to implement the course in daily practice. Third, other consortia will be invited to implement the program into regular care. Fourth, in the Netherlands, there are up to 100 GP caregiver groups who coordinate health care provided by the GP nurse (in Dutch: praktijkondersteuner huisartsen (POH)). One of these POHs is the mental health POH. The mental health POH is currently involved in diagnostic and (simple) therapeutic trajectories for patients with mental health problems. The mental health POH is also the designated person within primary care to inform patients about web-based interventions. Because midwives still have no access to these POHs, except after referring to the GP, we will invest in setting up programs to incorporate mental health care to pregnant women within the POH mental health care system. During the period of implementations, collaborative steps will be undertaken with the organization for POHs (in Dutch: Praktijkondersteuning Zuid-Oost-Brabant (PoZoB)) to implement this POH in perinatal mental healthcare. Principal investigator VP was one of the co-founders of PoZoB, and as the scientific adviser of PoZoB, he implemented the general mental health care program for the POH within PoZoB. Finally, it should be noticed that our society is increasingly familiar with the internet as a means to get access to all kinds of facilities. This means that every pregnant woman can get access to this online MBI by logging in into the website https://www.ontspannenzwanger.nl/. Once the effectiveness has been proven, the website will be more intensively promoted on the internet. Appropriate steps will be undertaken to make sure the website is easily accessible through the most common search engines.

Data output of current study will be published in international peer reviewed scientific journals to distribute the findings internationally. The first results of current study will become available in 2022.

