### Objectives and hypotheses

The aim of the current study is to test the effectiveness of an online MBI in pregnant women with pregnancy distress. The primary outcome is pregnancy distress, i.e. symptoms of depression and anxiety. Secondary outcomes are mindfulness skills, rumination and self-compassion, which are also seen as potential working mechanisms. Tertiary outcomes are obstetric data such as gestational age at birth, use of anesthesia, mode of delivery and birth weight. It is hypothesized that pregnancy distress in women who participate in the 8-week online MBI course (intervention group) will be significantly reduced compared to a control group, who does not complete this course and receives care as usual. With regard to the secondary outcomes, it is hypothesized that the intervention will lead to improvements in mindfulness skills and self-compassion, and a decrease in rumination for the intervention group. We will investigate whether the potential working mechanisms, i.e. mindfulness skills, rumination and self-compassion, are associated with a reduction in pregnancy distress in the intervention group.

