## Method/design

### Design and setting

The current study is a parallel group, two-arm, superiority randomized controlled trial (RCT) with equal allocation of participants and a repeated measures design. Table 1 shows the overall study design. The trial is part of a large longitudinal cohort study among pregnant women (The Brabant Study). Within the Brabant Study up to 4000 pregnant women are followed from 12 weeks of gestation until 8 to 10 weeks postpartum. The current trial targets a specific sub-group of pregnant women with symptoms of psychological distress, specifically depression and anxiety and is conducted in the South-East part of North-Brabant in the Netherlands. The trial is registered at clinicaltrials.gov (2018-CDE-9318) and was approved of by the Ethics Committee of the University of Amsterdam. Any trial amendments will be approved of by the Ethics Committee of the University of Amsterdam before implementation and will be reported to the trial registry.

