The women allocated to the intervention group will receive an information letter about the trial and the online MBI course by e-mail. Women will be asked to respond by e-mail whether they want to participate. When women agree to participate, they will sign a full written informed consent, which will be sent by post. After signing the informed consent, women will fill out questionnaires via internet, which will be around 16 weeks of pregnancy. Besides the standardized questionnaires, women will be asked whether they have had any previous experiences with mindfulness. Subsequently, women will start the 8-week online MBI course, followed between 16 and 28 weeks of pregnancy. Women in both the intervention and control group are not prohibited to partake in any other pregnancy course. At 28 weeks of pregnancy (post intervention) women in both groups will be asked whether they took part, or are still taking part, in adjunctive pregnancy courses, to be able to control for this variable in statistical analyses.

Participating women fill out online questionnaires at different time points during pregnancy as shown in Table 2. Women in the intervention and control group fill out the questionnaires of the Brabant Study at baseline (12 weeks of pregnancy), halfway through the intervention (20 weeks of pregnancy) and post intervention (28 weeks of pregnancy). Moreover, women in the intervention group fill out extra questionnaires before intervention (16 weeks of pregnancy), halfway through the intervention, post intervention and after a follow-up period of 8 weeks (36 weeks of pregnancy).

**Table 2 Tab2:** Measurements and time points

	Concept	Questionnaire	Measurement time points											
			12 weeks		16 weeks		20 weeks		28 weeks		36 weeks		Childbirth	
			I	C	I	C	I	C	I	C	I	C	I	C
Primary	Pregnancy distress	EDS	X	X			X	X	X	X	X			
	Pregnancy distress	TPDS (NA)	X	X			X	X	X	X	X			
Secondary	Mindfulness skills	TFMQ-SF			X				X		X			
	Rumination	RRQ			X				X		X			
	Self-compassion	SCS-SF			X				X		X			
Tertiary	Obstetric data	Non-standardized											X	X
	Demographic data	Non-standardized	X	X										
	Evaluation intervention	Non-standardized							X		X			

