### Statistical analyses

The baseline characteristics of completers and drop outs during follow-up will be compared by means of an independent t-test for continuous data and by Chi Square analysis for categorical data. Any significant differences (*p* < 0.05) in baseline characteristics between intervention and control group will be controlled for in the subsequent analyses. All analyses will be based on the intention-to-treat principle.

For the main analyses, multilevel regression models for repeated measures (mixed models) will be used to evaluate changes in primary outcome variables across time between intervention and control group and to evaluate changes in secondary outcomes across time in the intervention group. Temporal associations between change in secondary outcomes that may be potential mechanisms and change in primary outcomes will be examined by linear regression analyses, in which decrease in primary outcome scores are predicted by earlier changes in secondary outcome scores (and vice versa to control for potential reversed effects). Tertiary outcomes will be compared between intervention and control group using independent t-tests for continuous data and Chi Square analyses for categorical data.

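### The secondary hypothesis claims an effect of the course, but the three scales are measured and tested only in intervention-arm women who agreed to take it

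*Protocol article*

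**What the plan says.** - **Hypothesis** (Protocol article, Objectives and hypotheses): "it is hypothesized that the intervention will lead to improvements in mindfulness skills and self-compassion, and a decrease in rumination for the intervention group".
- **Design** (Design and setting): the trial is a "parallel group, two-arm, superiority randomized controlled trial (RCT) with equal allocation of participants".
- **Who is measured** (Procedure): "women in the intervention group fill out extra questionnaires before intervention (16 weeks of pregnancy" and again later. This happens after they have signed consent for the course. Table 2 marks the TFMQ-SF, RRQ and SCS-SF at 16, 28 and 36 weeks in the intervention columns only.
- **Analysis** (Statistical analyses): mixed models are used "to evaluate changes in secondary outcomes across time in the intervention group". The link between these scales and distress is examined by regressions described as temporal associations.
- **Limitation** (Discussion): the secondary outcomes "can only be explored in the intervention group", because controls complete only the cohort questionnaires, "in which mindfulness skills, rumination and self-compassion are not measured".

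**The concern.** The hypothesis is about what the course causes, while the planned contrast is an uncontrolled before-and-after change. Three other explanations enter that change in full:

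- natural change between 16 and 36 weeks of pregnancy;
- regression to the mean that is still under way at 16 weeks, since women enter on high distress scores at 12 weeks;
- self-selection, since the scales are completed only by women who agree to the course, expected to be about 35% of those allocated to it.

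If the plan is followed as written, a significant time effect supports the stated hypothesis even when the course did nothing to these skills. This concerns every outcome labelled secondary. A later analysis plan cannot repair it, because the control data will not exist.

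**Working it through.** **1. Setting the statements side by side.** The hypothesis says the intervention will lead to change. A test of that needs an estimate of what would have happened without the intervention. Table 2 provides no control value on any of the three scales at any time, so no between-arm contrast can be computed. What can be computed is the mean change among consenting intervention women, which equals course effect plus natural change plus residual regression to the mean. It is also estimated in a self-selected group.

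**2. The plan's own figures.** Sample size calculation: 400 × 0.35 = 140 consenting, and 140 × 0.85 = 119 completing. This reproduces. The total of 206 also reproduces: a repeated-measures MANOVA interaction with f = d/2 = 0.25, two groups, three time points and an assumed alpha of 0.05 gives power 0.901 at 206 and 0.899 at 205. That calculation concerns the primary time-by-group interaction. The article gives no figure for the secondary hypothesis.

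**3. How often drift alone would be significant (illustration).** From the article: n = 119. Assumed, because the article gives neither: drift δ in SD units and correlation ρ between the before and after scores. The test is approximated by a two-sided 0.05 paired t-test; the plan itself uses a mixed model.

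SD of change = √(2(1 − ρ)); noncentrality = δ√119 / √(2(1 − ρ)), with 118 df.

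| ρ | SD of change | δ = 0.1: noncentrality, P(significant) | δ = 0.2: noncentrality, P(significant) |
|---|---|---|---|
| 0.5 | 1.000 | 1.09, 0.19 | 2.18, 0.58 |
| 0.6 | 0.894 | 1.22, 0.23 | 2.44, 0.68 |
| 0.7 | 0.775 | 1.41, 0.29 | 2.82, 0.80 |

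With no course effect and no drift, the probability would be 0.05.

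**4. What a valid between-arm comparison would look like.** Randomisation comes before consent to the course, and only intervention women are asked for that consent (Procedure). Comparing 119–140 consenters with all controls would therefore not be a randomised comparison. The comparison has to include the 400 − 140 = 260 women expected to decline. Assuming 400 analysed per arm, 35% uptake and no effect in decliners, the effect is diluted to 0.35d, with noncentrality 0.35d × √(400/2):

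- d = 0.32 among consenters (the mindfulness effect quoted from the meta-analysis in the Background): 0.112 × 14.14 = 1.58, power about 0.35.
- d = 0.5 among consenters: 0.175 × 14.14 = 2.47, power about 0.70.

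**The case against.** The strongest reply is that the plan is open and largely consistent. The Discussion names one-arm measurement as a limitation, gives the reason and speaks of exploring. The hypothesis carries the words *for the intervention group*, the analysis says the same, and nothing promises a between-arm test. All of that is correct, and it limits the point to what is claimed rather than what is hidden. It does not remove it. Leading to an improvement is a statement of effect, and the limitation neither withdraws it nor says that it cannot be tested against control.

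Three stronger readings are tempting and not supported:

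- **That the plan claims mediation.** A reader might infer this from the talk of working mechanisms. The Objectives ask only whether the scales are associated with reduced distress in the intervention group, and the Statistical analyses refer to temporal associations, with reverse-direction models. Mediation appears only in descriptions of earlier literature.
- **That the size of regression to the mean can be derived from upper-quartile selection.** Entry is EDS > 7 and/or TPDS negative affect > 9, with EDS > 18 excluded. That is not a single untruncated upper quartile. The first secondary measurement also comes about four weeks after selection, so some regression has already happened. The article does not give the correlations needed.
- **That giving controls the scales at 28 weeks would by itself make the comparison randomised.** It would not, for the reason in step 4 of the working.

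It is also fair that the article does not show whether the cohort questionnaire can carry more items. Controls consented to the cohort study only.

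**Conclusion.** The point holds: the secondary hypothesis and its test are wrong as written. They state and test an effect of the course using data that can only describe change among women who took it up. This structural conclusion needs no assumed number. The size does: with 119 completers, ρ of 0.5–0.7 and a paired-t approximation, a drift of 0.1 SD unrelated to the course would be significant about 19–29% of the time, and 0.2 SD about 58–80%. These figures are illustrative, since the article gives no information on how much the scales drift.

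The between-arm test of the primary outcome does not depend on these scales and is not affected. The mechanism analysis is already stated as association and can stay on those terms.

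**What to change.** **Main change.** Reword Objectives and hypotheses and Statistical analyses so that mindfulness skills, rumination and self-compassion are a descriptive, exploratory estimate of within-arm change with confidence intervals. State that the change is not attributed to the intervention, and keep the mechanism regressions as associations. The cost is wording only.

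**Optional, if the cohort can carry it.** Add the three scales (15 + 12 + 12 = 39 items) to the 28-week online questionnaire for all randomised women in both arms, including intervention-arm women who declined the course, and compare the arms by intention to treat. With 28 women enrolled at the protocol date, most of the data could still be collected. The costs are an ethics amendment, extra questionnaire burden, no data from women already past 28 weeks, and the dilution shown in the working (power about 0.35 to 0.70 under those assumptions). The effect hypothesis could then stay, tested by that comparison and with its limited power stated.

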### Intervention

The online MBI course is based on existing protocols of the Mindfulness-Based Stress Reduction (MBSR) as described by Kabat-Zinn [51] and Mindfulness-Based Cognitive Therapy (MBCT) as described by Segal et al. [52]. It consists of eight one-hour sessions including psycho-education about the mechanisms of stress, coping, and relaxation, especially related to pregnancy, practicing mindfulness skills (i.e. mindful breathing, mindful moving, observing and letting go of thoughts and emotions with a non-judgmental attitude), sharing experiences, and completing home assignments. The sessions have been developed specifically for pregnant women and acknowledge pregnancy-related distress. Table 3 shows a short overview of the online MBI course. The website of the course can be viewed at https://www.ontspannenzwanger.nl/. Within the current study, the course will be offered free of charge to participating women. As far as we know, there are no known risks of the intervention to pregnant women.

**Table 3 Tab3:** Content of online MBI course ‘Ontspannen zwanger’ (In English: ‘Relaxation in pregnancy’)

Week	Session
1	**Stress and Mindfulness** Exercises in online session: bodyscan Home assignments (daily): bodyscan, routine activity, activity awareness
2	**Dealing with obstacles, a different view** Exercises in online session: mindful breathing Home assignments (daily): bodyscan, mindful breathing, logbook pleasant events
3	**The body and the senses** Exercises in online session: mindful yoga, 3 min breathing space Home assignments (daily): bodyscan/yoga, 3 min breathing space, routine activity, logbook unpleasant events
4	**Thoughts** Exercises in online session: observing thoughts, mindful walking Home assignments (daily): bodyscan/yoga/sitting meditation, 3 min breathing space, routine activity
5	**Emotions** Exercises in online session: working with emotions Home assignments (daily): sitting meditation/bodyscan/yoga, 3 min breathing space, routine activity, logbook stressful communication
6	**Communication and awareness** Exercises in online session: conscious communication, mindful breathing and open awareness, sounds and open awareness Home assignments (daily): sitting meditation/bodyscan/yoga, 3 min breathing space, routine activity, conscious communication

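### The trial course appears open to any pregnant woman during the trial, and the 28-week course question is not shown to identify controls who use it

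*Protocol article*

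**What the plan says.** Under Objectives and hypotheses, the intervention group is compared with "a control group, who does not complete this course and receives care as usual".

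The Intervention section prints the course's web address ("The website of the course can be viewed at") and says of its cost: "Within the current study, the course will be offered free of charge to participating women". The dissemination part of the Discussion states: "This means that every pregnant woman can get access to this online MBI by logging in into the website". It adds: "Once the effectiveness has been proven, the website will be more intensively promoted on the internet".

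On other courses, the Procedure section says: "Women in both the intervention and control group are not prohibited to partake in any other pregnancy course". At 28 weeks both groups are asked "whether they took part, or are still taking part, in adjunctive pregnancy courses". The stated purpose is to allow adjustment for the answer in the analysis.

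Table 2 schedules the course evaluation and the mindfulness, rumination and self-compassion scales for the intervention arm only. The count of sessions completed belongs to that evaluation. Nothing in the article bars controls from the website or describes another record of their use of it.

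**The concern.** The trial estimates the effect of offering the course against care as usual. A control woman who finds and follows the same course receives the treatment under test, and under intention to treat she still counts as a control. If the course works, this pulls the estimate toward no difference.

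Some crossover can be tolerated if it is known. The difficulty is that the only item described asks about adjunctive courses in general. Two consequences follow:

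- **Interpretation.** With a small or null result, the investigators could not tell whether the course did little or whether some controls had also used it.
- **Adjustment.** If trial-course use is reported under the general item, it shares one covariate with ordinary antenatal classes. That variable is measured after randomisation and may itself depend on allocation. Adjusting for it in the main model changes the question being answered and can bias the estimated effect.

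**Working it through.** **1. Is the course accessible during the trial?** The Discussion describes access in the present tense. Promoting the site more intensively after proof implies that it is already public. The Intervention section gives the address. Trial status reports 28 women enrolled on 20 February 2020, and the Discussion expects first results in 2022, so most control follow-up lay ahead. Access during the trial is thus a fair inference, though not an explicit statement.

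**2. What would record control use?**

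| Source of information | Intervention | Control |
|---|---|---|
| Sessions completed and course evaluation (Table 2) | yes | no |
| Mindfulness skills (Table 2) | yes | no |
| 28-week question on adjunctive courses (Procedure) | yes | yes |

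Only the last row reaches controls. The permission for other courses and the word adjunctive both point most naturally to courses besides the trial's own. A control who used the trial course might report it or might not.

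**3. The plan's own sample size.** Inputs from Sample size calculation: d = 0.5, time-by-group interaction in a MANOVA, three time points, two groups, power 0.90, total 206. Alpha is not stated there; 0.05 is assumed.

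- f = d/2 = 0.25
- df1 = (2 − 1)(3 − 1) = 2; df2 = N − 3 = 203
- Noncentrality = N × f² = 206 × 0.0625 = 12.875
- Power from the noncentral F distribution = 0.901; the smallest N reaching 0.90 is 206

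The stated figure is reproduced exactly. It contains no allowance for crossover.

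**4. Illustration of dilution.** Let c be the share of controls who take the course and gain its full effect. Then the diluted effect is 0.5 × (1 − c), and f is half of that. The documents give no value for c, so every non-zero row is an assumption.

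| c | d | 206 × f² | Power at N = 206 | N for power 0.90 |
|---|---|---|---|---|
| 0% | 0.500 | 12.88 | 0.901 | 206 |
| 5% | 0.475 | 11.62 | 0.867 | 228 |
| 10% | 0.450 | 10.43 | 0.826 | 254 |
| 20% | 0.400 | 8.24 | 0.724 | 320 |

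With 103 controls, 5% is about 5 women and 10% about 10. If a control using the course alone gained only half the effect, c = 10% would act like the 5% row, since 0.5 × (1 − 0.10 × 0.5) = 0.475.

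**The case against.** Several points on the other side stand.

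- **Crossover may be rare.** Only intervention women are sent the letter about the trial and the course. Access is by log-in, and free use is stated only for participating women. Even among women invited directly, the plan expects only 35% to consent. This lowers the likely rate but does not measure it.
- **The item's wording is not shown.** The article paraphrases one question from a longer questionnaire. It goes to both arms and covers past and current courses, and the trial course is itself a pregnancy course. A reader might infer that crossover would go undetected. The documents do not support that; they show only that detection is not assured by the item as described.
- **The full effect is generous to the concern.** The Intervention section calls contact with the online trainer important, and a control using the site alone would probably lack it.

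Two stronger readings are tempting and should be resisted.

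- The plan "to inform all healthcare workers about the online MBI course" in the local area could be read as roll-out during control follow-up. The Discussion introduces that step as one of five ways to distribute study results and derived knowledge, so in context it follows the results.
- Setting control use against the 35% expected uptake makes the proportional loss of contrast look much larger. That comes mainly from seeking consent after randomisation, which is a separate issue and does not measure crossover.

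**Conclusion.** The concern holds as a limited one. The trial course appears to be publicly accessible during the trial, nothing described restricts control access, and the single item described is not shown to distinguish trial-course use from other pregnancy courses. Crossover may be under-recorded or absorbed into a general covariate, and any resulting dilution could not be assessed.

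The size is unknown. At assumed rates of 5% or 10% with full effect, power at 206 women falls from 0.90 to about 0.87 or 0.83. These figures rest on the plan's own MANOVA model, alpha 0.05, and the full effect in the whole intervention arm. They are not a forecast. The documents do not show that crossover is happening or that it would be missed.

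**What to change.** 1. In the existing 28-week questionnaire, after the EDS and TPDS, ask both arms separately about (a) online mindfulness courses in pregnancy, including the trial's own, (b) other mindfulness courses or apps, and (c) other pregnancy courses. If the full questionnaire already does this, say so.
2. Report each type of exposure by arm.
3. Keep the as-randomised analysis primary and do not adjust it for course use, which arises after randomisation. Use exposure only descriptively or in a sensitivity analysis.

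The cost is two or three more items in a questionnaire that both arms already complete. Placing them after the distress scales protects the 28-week primary outcome. One small downside remains: naming the course may alert some controls to it before childbirth, when the tertiary obstetric outcomes are collected in both arms.
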